#### Analysis of Primary Endpoints

Summary of EPG will be provided by diagnostic method, STH species, and timepoint. A permutation test (5,000 iterations) will be employed for comparison of EPG between different diagnosis methods (KK1.0 and KK2.). The 95% CI will be determined based on bootstrap analysis (5,000 iterations). To preserve the correlation of egg count readings by different diagnostic methods from either different samples or same smear of the same participant, permutations will be done within each participant, not across all participants (ie, in a permutation, once an egg count

reading is randomly assigned to one of the 2 diagnostic methods, the other reading from the same participant will be automatically assigned to the other diagnostic method). Re-sampling in bootstrap will be performed at participant level, and the egg count reading will remain with the same diagnostic method as performed.

Sensitivity for KK1.0 at 30 minutes will be calculated as

$$= \frac{N(KK(1.0(+))_{30m})}{N(+)}$$

Where  $N(KK1.0(+))_{30m}$  is the number of positive samples based on KK1.0 method at 30 minutes. Sensitivity for other diagnostic methods and other timepoints will be calculated similarly.

A permutation test (5,000 iterations) will be employed for comparison of sensitivity between different diagnosis methods and the 95% CI will be determined based on bootstrap analysis (5,000 iterations) in similar approach as for EPG. Sensitivity will be calculated for each of the 5,000 iterations, and p-value and 95% CI will be constructed.

Summary of percentages of SAC with low, moderate, or heavy infection intensity will be provided.

2x2 (eggs, no eggs) and 3x3 (low, moderate, or heavy infection intensity) tables based on egg load will be provided to evaluate agreement between different test methods. Weighted Kappa statistics will be provided.

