### **3.3. Patient Population**

School-aged children in selected STH endemic areas of Ucayali, a remote Amazonian region of Peru is the target patient population in this study. The study will focus on SAC (age 5–14) since they have a higher burden of STH infection and are a major target of PC programs for treating STH. An informed consent will be obtained from parents of SAC, aged 5-14 years, and an additional assent will be obtained from SAC older than 8 years. All SAC in a household encounter by the field worker will be asked to provide a fresh stool sample.

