### **4.1. Determination of Sample Size**

The study is designed to generate descriptive data for informative purpose. No formal hypotheses will be tested. The planned sample size of 500 children is based on pragmatic considerations.

The sample size will be based on enrolling SAC in the in selected STH endemic areas of Ucayali, a remote Amazonian region of Peru. The sample size is considered adequate to evaluate an improved diagnostic method (KK2.0) over the standard of testing for monitoring STH prevalence in LATAM.

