### 4.3. Data Analyses

#### 4.3.1. Data Analyses

Descriptive summaries will be provided by diagnostic method and STH species. All continuous variables will be summarized using descriptive statistics, which will include the number of children, mean, standard deviation, median, minimum, and maximum. A 95% confidence interval (CI) will also be provided for EPG and sensitivity. All categorical variables will be summarized using frequencies and percentages. Summary and analysis will be provided by diagnostic method, STH species, and timepoints (30 minutes and 24 hours). It should be noted that at the 24±4-hour timepoint the same slide (Slide B), will be evaluated by both the KK1.0 and KK2.0 methods. While at the 30-minute timepoint, different slides (slides A and B) from the same stool sample will be evaluated by the same 2 methods. Therefore, extra caution should be exercised when comparing results from the different methods at the 30-minute timepoint since 2 different slides are being analyzed.

Egg load will be classified into 3 intensity categories as detailed below according to EPG:

- *A. lumbricoides*: Low: <5,000 EPG; Moderate: 5,000-49,999 EPG; Heavy: >50,000 EPG
- *T. trichiura*: Low: <1,000 EPG; Moderate: 1,000-9,999 EPG; Heavy: >10,000 EPG
- Hookworms: Low: <2,000 EPG; Moderate: 2,000-3,999 EPG; Heavy: >4,000 EPG

Since TSET method cannot produce EPG, intensity of each STH species will only be derived for KK1.0 and KK2.0 methods.

Since no “gold” standard for egg counts exist in this study, a diagnostic pseudo “gold” standard will be created. A sample is considered to be truly positive if any diagnostic method comes back with a positive reading at any time of the study.

Number of total positive samples for a STH species is defined as

$$N(+) = N(KK1.0(+))_{30m} \cup KK2.0(+))_{30m} \cup KK1.0(+))_{24h} \cup KK2.0(+))_{24h} \cup TSET(+))$$

Where  $KK1.0(+))_{30m}$  indicates a positive sample based on KK1.0 at 30 minutes,  $KK2.0(+))_{30m}$  indicates a positive sample based on KK2.0 at 30 minutes,  $KK1.0(+))_{24h}$  indicates a positive sample based on KK1.0 at 24 hours,  $KK2.0(+))_{24h}$  indicates a positive sample based on KK2.0 at 24 hours, and  $TSET(+))$  indicates a positive sample based on TSET which is performed only once during the study.

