### 8.3. Source Documentation

The primary data sources for this study will be the Demographic Data Collection Form ([Attachment 2](#)) for each child collected at their home (Visit 2) by the field worker and the Sample Processing Form ([Attachment 1](#)) for the stool sample analyses done at the laboratory by the technician. All data will be entered in the eCRF by the lab coordinator, who is an expert lab technician.

The type and level of detail of source data available for a child should be consistent with that commonly recorded by participating study personnel as a basis for routine clinical practice. Specific details required as source data for the study will be reviewed with the participating physician before the study.

The following data collected in the Demographic Data Collection Form will be recorded into the eCRF in addition to the data in the Sample Processing Form by the lab coordinator:

- Demographics (age, gender)
- School grades
- Number of SAC in the household

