**Attachment 2: Demographic Data Collection Form****Parasitology AI Study Peru**

|                              |  |                                      |  |                         |  |
|------------------------------|--|--------------------------------------|--|-------------------------|--|
| Area
(A,B,C,D,E,F) |  | Field Worker
(A,B,C,D,E,F) |  | QRC ID
Code # |  |
|------------------------------|--|--------------------------------------|--|-------------------------|--|

|                                    |                                                 |
|------------------------------------|-------------------------------------------------|
| Information Collection Date | ____ / ____ / 2022 (use format: dd / mm / 2022) |
|------------------------------------|-------------------------------------------------|

|                        |                                                                        |                                                                                                                                                   |                                                                                                                                                 |
|------------------------|------------------------------------------------------------------------|---------------------------------------------------------------------------------------------------------------------------------------------------|-------------------------------------------------------------------------------------------------------------------------------------------------|
| Child full Name |                                                                        |                                                                                                                                                   |                                                                                                                                                 |
| Age             | Gender                                                          | School Grade                                                                                                                               | Are there OTHER children between 5-14 years in the house?                                                                                |

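### Siblings are sampled together but the bootstrap resamples single children and no household identifier is listed, so the EPG confidence intervals will be too narrow if egg load clusters in households

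*Protocol*

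**What the plan says.** **Recruitment.** Field workers survey areas A to F for homes with children aged 5 to 14, then visit those homes. Section 3.3 of the protocol states: "All SAC in a household encounter by the field worker will be asked to provide a fresh stool sample". No limit per household is given, and section 4.1 says only that "The planned sample size of 500 children is based on pragmatic considerations".

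**Intervals.** Section 4.3.1 states that "A 95% confidence interval (CI) will also be provided for EPG and sensitivity", with summaries by method, species and timepoint. The Analysis of Primary Endpoints sets 5,000 bootstrap iterations and names the unit: "Re-sampling in bootstrap will be performed at participant level, and the egg count reading will remain with the same diagnostic method as performed". The one correlation the protocol addresses is between readings on the same child. For the permutation test, "permutations will be done within each participant, not across all participants".

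**Household data.** The demographic items that section 8.3 sends to the eCRF include "Number of SAC in the household". Attachment 2 asks "Are there OTHER children between 5-14 years in the house", with the answers none, 1, 2, or 3 or more. The identifier in section 8.2 is a QR code generated at the laboratory, and nothing described there ties it to a household. No legible field on either form is a household code. Clustering by household or area is not mentioned.

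**The concern.** Children in one home share water, soil, sanitation and treatment history, so infection status and egg load may well be alike among siblings. The household is what the field worker reaches, and the children come with it. A bootstrap that draws children one at a time treats siblings as independent and so understates the variance of any average over all children when the within-household correlation is positive.

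Mean EPG by method is such an average. EPG is the first-listed primary endpoint and has a promised 95% interval. In a study that tests no hypotheses, the intervals are the main statement of uncertainty.

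The resampling unit is fixed in the protocol itself, so this is not a detail left to an analysis plan that is not shown here. It is also partly a data-capture issue: a later plan could change the unit only if the data showed which children live together.

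**Working it through.** The protocol states no precision target, prevalence, household size or ICC, so there is no figure of its own to reproduce. From the protocol come N = 500, the child as resampling unit and the 95% level. Everything else below is assumed.

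**1. Closed form for a mean over all children**

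With m children per household:
- Design effect: DE = 1 + (m − 1) × ICC
- Correct width / planned width = √DE
- True coverage of a nominal 95% interval = 2Φ(1.96/√DE) − 1

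| m | ICC | DE | Width ratio | Coverage |
|---|---|---|---|---|
| any | 0 | 1.00 | 1.00 | 95.0% |
| 1.5 | 0.1 | 1.05 | 1.02 | 94.4% |
| 1.5 | 0.4 | 1.20 | 1.10 | 92.6% |
| 2 | 0.2 | 1.20 | 1.10 | 92.6% |
| 2 | 0.4 | 1.40 | 1.18 | 90.2% |
| 3 | 0.2 | 1.40 | 1.18 | 90.2% |
| 3 | 0.4 | 1.80 | 1.34 | 85.6% |

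Worked example, m = 2 and ICC = 0.2: DE = 1 + 1 × 0.2 = 1.20; √1.20 = 1.095; 1.96/1.095 = 1.79; coverage 92.6%. For a plain mean, 500 children then act like 500/1.20 = 417.

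**2. Simulation of the planned bootstrap against a household bootstrap**

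Each data set had 500 children. Households held 1, 2, 3 or 4 children in assumed shares of 35/35/20/10%, a mean of 0.35 + 0.70 + 0.60 + 0.40 = 2.05. A latent intensity was correlated within household at 0.2 or 0.4, and counts were Poisson given that intensity. Two Kato-Katz readings and one sedimentation reading formed the composite standard (a simplification of the protocol's five readings). There were 600 data sets per setting, 400 resamples each, and two intensity settings (true prevalence about 48% and 30%).

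Ratio of household to participant interval width:

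| Estimate | Correlation 0.2 | Correlation 0.4 |
|---|---|---|
| Mean EPG | 1.04 to 1.07 | 1.11 to 1.15 |
| Sensitivity | 0.99 to 1.00 | 1.00 to 1.01 |
| Difference in EPG between methods | 0.99 to 1.00 | 0.99 to 1.00 |
| Difference in sensitivity between methods | 1.00 | 1.00 |
| Prevalence | 1.08 to 1.09 | 1.18 |

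Sensitivity barely moves because its denominator holds only positive samples: what matters is whether missed detections cluster among positives, not whether infection clusters. The paired differences barely move because siblings' shared level cancels within each child.

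**3. Two limits on the EPG result**

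- With far more skewed counts (mean EPG about 500) the EPG ratio was only 1.00 at correlation 0.2 and 1.03 at 0.4. There the percentile interval covered badly under either unit, at about 56% to 65%, and at about 60% even with no clustering, so skewness dominated.
- In the settings of step 2, coverage for mean EPG rose from 86–91% with child resampling to 90–92% with household resampling. Household resampling repairs the clustering part of the shortfall, not the part due to skewness.

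**The case against.** The case on the other side is strong on scope.

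**Sensitivity.** A reader might infer that every planned interval is too narrow, including the one for sensitivity, which section 2 names as the intent of the study. The documents do not support this. Sensitivity is defined only among samples positive by some method, so the correlation of infection across all 500 children is the wrong input, and the simulated change was about 1% or less. That result assumes detection clusters only through egg intensity. Shared handling of siblings' samples could add clustering, but the protocol gives no figure for it.

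**Prevalence.** It would be affected most, but no interval is promised for it.

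**Which EPG interval.** The bootstrap sentence follows directly on the comparison of methods and could be read as giving an interval for the difference, which clustering leaves almost unchanged. However, section 4.3.1 opens by promising an interval for EPG itself and no other interval method is given, so the concern stands for EPG by method.

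**Recovering households later.** A reader might infer that households could never be identified afterwards. That goes too far. Attachment 2 holds the child's name, area, field worker, date and number of other children; section 8.2 requires an enrollment log; and results are delivered to parents at Visit 4. Partial reconstruction may be possible by hand. What stands is that the listed eCRF data do not carry the link. The attachment tables are also broken in places, so the absence of a household field is judged from what is legible and from the list in section 8.3.

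**Consequences.** The study is descriptive, its sample size is pragmatic, and no decision rule depends on the intervals. This lowers the severity without removing the point.

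**Conclusion.** The point holds for the 95% intervals for EPG by method, and conditionally. They will be too narrow if households contribute more than one child and egg load is positively correlated within them. Recruitment makes the first condition likely; the second is plausible but undocumented.

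The size rests wholly on assumed inputs. The closed form spans 2% to 34%. The simulation with moderately skewed counts gives 4% to 15%, and with very skewed counts close to nothing. With no within-household correlation there is no error.

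A general loss of effective sample size for the whole study does not follow, because the design effect for a mean over all children does not carry over to sensitivity or to paired differences. Severity is minor to moderate.

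**What to change.** 1. Add a household number to Attachment 2 and to the list of eCRF items in section 8.3, assigned by the field worker at the home visit.
2. In section 4.3.1, make the household the bootstrap unit, keeping all children and all readings of a drawn household together.
3. If an interval for prevalence is reported, use the same unit.
4. Leave the within-child permutation scheme as it is. It exchanges two readings from the same child, so the shared household level drops out.

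Stratifying the bootstrap by area is optional. Area is already recorded on both forms, but the protocol describes no sampling quotas by area that would require it.

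The cost is one form field, a small change to the resampling code and somewhat wider EPG intervals. If siblings prove uncorrelated, the intervals will hardly change. The field is easy to add before enrollment; rebuilding households from names and logs afterwards would be laborious and possibly incomplete.

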Janssen GPH Research and Development (R&D) has been evaluating an artificial intelligence digital pathology (AI-DP) based on the KK thick-smear, to achieve WHO goal for the Diagnostic Target Profile of the STH as part of J&J contribution to 2030 NTD goals. The prototype unit has travelled for demonstration and field testing to Tanzania, Cambodia, Kenya, Ethiopia, Washington DC (COR-NTD Innovation Lab) and Belgium. During the course of evaluation, 7,780 field of view images (of approximately 800  $\mu\text{m}$  x 600  $\mu\text{m}$ ) were manually reviewed to verify image quality, image focus, locations and classes of STH eggs. A total of 16,990 parasite eggs have been marked-up and form the ground truth data for training artificial intelligence (AI) models. An open- source relational database built in MySQL (a database management system) manages the data and allows the custom AI-DP development pipeline.

The performance of the technology is summarized as follows:

- *Ascaris lumbricoides*: Sensitivity 96%, Specificity 98%, Precision 98%, Accuracy 97%
- *Trichuris trichiura*: Sensitivity 97%, Specificity 98%; Precision 93%, Accuracy 98%
- Hookworms (*Necator americanus* and *Ancylostoma duodenale*): Sensitivity 96%, Specificity 99%; Precision 97%, Accuracy 99% [1]

Since the frequency (ie, annually or bi-annually) of drug administration in PC programs are based on prevalence and intensity of infections, the AI-DP tool is a more sensitive diagnostic method and that can lead to more successful implementation of STH programs. The WHO has defined threshold criteria to describe low, moderate and heavy infection intensity and is presented below in [Table 1](#) [2].

**Table 1: Fecal Egg Count Thresholds Defining Low, Moderate and Heavy Infection Intensity [2]. The Fecal Egg Counts are Expressed as Eggs per Gram of Stool.**

|                             | Low     | Moderate     | Heavy   |
|-----------------------------|---------|--------------|---------|
| Ascaris lumbricoides | 1–4,999 | 5,000–49,999 | >50,000 |
| Trichuris trichiura  | 1–999   | 1,000–9,999  | >10,000 |
| Hookworms                   | 1–1,999 | 2,000–3,999  | >4,000  |

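### The bootstrap 95% CI fixed for each method's sensitivity has zero width when a method detects all (or none) of a species' positives, and undercovers when positives are few and sensitivity is high

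*Protocol*

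**What the plan says.** Section 4.3.1 promises an interval for the endpoint: "A 95% confidence interval (CI) will also be provided for EPG and sensitivity". Under Analysis of Primary Endpoints it fixes the method: "the 95% CI will be determined based on bootstrap analysis (5,000 iterations) in similar approach as for EPG". The resampling unit is also fixed: "Re-sampling in bootstrap will be performed at participant level", with each reading kept with the method that produced it. The text then adds: "Sensitivity will be calculated for each of the 5,000 iterations, and p-value and 95% CI will be constructed".

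Sensitivity is the number of samples positive by the method divided by N(+). The reference behind N(+) is a union of five readings: "A sample is considered to be truly positive if any diagnostic method comes back with a positive reading at any time of the study". Results are reported separately by method, species and timepoint, so each species has its own N(+).

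Section 4.1 says of the sample size: "The planned sample size of 500 children is based on pragmatic considerations". The protocol states no species prevalence, expected N(+) or minimum N(+). It names no bootstrap type and no alternative interval for estimates at 0% or 100%.

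**The concern.** A bootstrap can only reproduce variation that is present in the sample. If a method misses none of the N(+) samples, the data contain no misses to resample, and the procedure reports no uncertainty. Just below 100% the interval also relies on very few misses and tends to be too short.

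The study is descriptive, so its intervals are the main statement of how strong the evidence is. A result such as 100% (95% CI 100-100) from 10 or 20 positives would claim certainty that the data cannot give, for the tool the study is meant to support. Section 3.1.1 says hookworm eggs clear from the sample early, so the opposite boundary, 0%-0% at 24 hours, is also possible.

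**Working it through.** **Inputs.** From the protocol: 500 children (4.1); 5,000 participant-level resamples and a 95% level (4.3.1); sensitivity = x/N(+), where x is the number detected by the method (4.3.1). The protocol has no figure of its own to reproduce. Assumed: N(+) = 10, 20, 30, 50 (2%, 4%, 6%, 10% of 500); true sensitivity s = 0.96, 0.90, 0.80; children independent.

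**Step 1: the boundary.** In resample b, sensitivity is S_b = D_b/M_b. M_b counts the resampled children who are reference-positive and D_b counts those also detected. If x = N(+), then D_b = M_b and S_b = 1 in every resample that contains a positive.
- Percentile limits: [1, 1].
- Basic limits: 2×1 − 1 = 1 at both ends.
- BCa limits: quantiles of a constant, [1, 1].

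If x = 0, the same argument gives [0, 0]. More iterations change nothing.

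For comparison, with all detected the Clopper-Pearson lower limit is 0.025^(1/N(+)) and the Wilson lower limit is N(+)/(N(+) + 3.84).
- 10 of 10: 0.692 and 0.722.
- 20 of 20: 0.832 and 0.839.

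**Step 2: chance of collapse at 100%.** This is s^N(+). For example, 0.96^20 = 0.442.

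**Step 3: coverage.** Sum the Binomial(N(+), s) probability over every x whose interval contains s. Percentile limits are the 2.5% and 97.5% quantiles of Binomial(N(+), x/N(+)), divided by N(+).

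Example, N(+) = 20 and s = 0.96:

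| x | Probability | Percentile interval | Contains 0.96? |
|---|---|---|---|
| 20 | 0.442 | 1.00-1.00 | no |
| 19 | 0.368 | 0.85-1.00 | yes |
| 18 | 0.146 | 0.75-1.00 | yes |
| 17 | 0.036 | 0.70-1.00 | yes |
| 16 | 0.006 | 0.60-0.95 | no |

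Coverage = 0.368 + 0.146 + 0.036 ≈ 0.55. Almost all of the loss comes from the collapse at x = 20.

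Full results:

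| s | N(+) | Chance of 100%-100% | Percentile bootstrap coverage | Wilson coverage |
|---|---|---|---|---|
| 0.96 | 10 | 66.5% | 33.5% | 94.2% |
| 0.96 | 20 | 44.2% | 55.1% | 95.6% |
| 0.96 | 30 | 29.4% | 70.5% | 96.9% |
| 0.96 | 50 | 13.0% | 86.7% | 95.1% |
| 0.90 | 10 | 34.9% | 65.0% | 93.0% |
| 0.90 | 20 | 12.2% | 87.6% | 95.7% |
| 0.90 | 30 | 4.2% | 95.0% | 97.4% |
| 0.90 | 50 | 0.5% | 95.7% | 97.0% |
| 0.80 | 10 | 10.7% | 88.6% | 96.7% |
| 0.80 | 20 | 1.2% | 92.1% | 95.6% |
| 0.80 | 30 | 0.1% | 94.6% | 96.4% |
| 0.80 | 50 | <0.1% | 93.8% | 95.1% |

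**Step 4: does the unnamed bootstrap type matter?** The plan was also simulated as written: 500 children, 5,000 resamples, N(+) varying between resamples. At s = 0.96 and N(+) = 10/25/50, coverage was:
- percentile 33.5/63.7/86.7%
- basic 33.5/63.9/86.9%
- BCa 33.5/62.3/85.6%

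At s = 0.96 the percentile shortfall is still visible at N(+) = 100 (90.6%) and essentially gone at 200 (94.5%). Wilson is not perfect either (92.4% at N(+) = 25, s = 0.96), but it never collapses. Clopper-Pearson stays above 95% throughout.

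**The case against.** The strongest reply is that this is a corner case. It needs few positives and high sensitivity together, and low prevalence supplies only the first. The protocol recruits in areas it calls endemic, and a union of five readings enlarges N(+). At 80% sensitivity and 20 positives, the chance of collapse is about 1%. This stands, and it limits the likelihood of the problem.

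A reader might infer that the study should expect to be near the boundary because section 1.1 reports, for hookworm, "Sensitivity 96%, Specificity 99%; Precision 97%, Accuracy 99" percent, and 96-97% sensitivity for the other species. The documents do not support that step. Those figures follow a description of reviewed field-of-view images and marked-up eggs used to train AI models. The study's sensitivity is per stool sample, against two slides, two timepoints and TSET. One reading of Slide B can miss a child who is positive only on Slide A or TSET, however well the AI recognises eggs. Section 1.3 also says conventional Kato-Katz is insensitive for light infections, and KK2.0 reads the same kind of smear.

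A second reply is that results are exploratory, section 4 is only a general description, and a boundary rule could sit in an SAP that is not shown. An SAP could indeed add one. But the protocol already fixes the bootstrap as the method, and the intervals carry the evidence when no hypothesis is tested.

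A reader might also extend the point to household clustering or to the KK2.0-minus-KK1.0 difference. The documents give no design effect, the visible forms show no household identifier, and no defect was shown for the paired comparison. Neither extension is made here.

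**Conclusion.** The point holds as a conditional defect. The collapse at 0% and 100% is algebra and needs no assumption. The undercoverage depends on N(+) and sensitivity, which the protocol does not give. It is severe at 96% with up to about 30 positives, marked at 90% with 20 or fewer, and largely gone at 80% by about 20 to 30 positives.

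No clean safe threshold should be read from these values, because coverage moves irregularly with N(+): at 85% it is 95.5% for 20 positives but 88.1% for 25. The documents do not show that any species will be rare in Ucayali or that any method will be near 100%. They also do not exclude either, and the plan as written has no safeguard if both occur. It is worth correcting before analysis, but it does not invalidate the design.

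**What to change.** In section 4.3.1, replace the bootstrap interval for each single-method sensitivity with a Wilson or Clopper-Pearson interval, and print N(+) beside every sensitivity estimate. Clopper-Pearson is the conservative choice; Wilson is shorter, with coverage close to nominal. Keep the participant-level bootstrap for EPG and for the paired KK2.0-minus-KK1.0 comparison. Carry the same wording into the synopsis if it names the interval, and into the SAP.

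The cost is one sentence and standard software, with no change to data collection. The downside is wider intervals when N(+) is small, for example 83%-100% (Clopper-Pearson) instead of 100%-100% when 20 of 20 are detected.
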